#### Comparison between good gaze response group and poor gaze response group

Concerning group comparison between two subgroups of ASD based on gaze response during joint attention tasks, several elements will be investigated. These include socio-demographic and clinical characteristics, social gaze patterns (gaze frequency towards or away from foci of attention). Furthermore, structural MRI profiles comprising of cortical thickness and surface area, intensity contrast, and geodesic distance, as well as rsfMRI profiles detailing stepwise functional connectivity difference, will be assessed.

Continuous variables will be represented using means, standard deviations, medians, and ranges. To compare categorical variables, the chi-squared test will be utilized. All statistical analyses and computations of the validation measures will be conducted using Python 3.6.8, in conjunction with SciPy version 1.4.1 (https://docs.scipy.org/doc/scipy-1.4.1/) and Statsmodels 0.11.1 (https://www.statsmodels.org/dev/release/version0.11.1.html). A p-value < 0.05 will be used as the threshold for statistical significance.

#### Power calculation – sample size estimation

For this exploratory study, the lack of preceding data precludes the establishment of a definitive sample size. Nevertheless, referencing guidelines for comparable studies, we advocate a minimum sample size of 12, considering the study’s feasibility, precision of means and variances, and compliance with regulatory requirements [44]. Reflecting on a previous investigation that effectively classified three distinct severity subclasses of ASD with a cohort of 45 individuals [25], our study plans to recruit 60 participants. This number takes into consideration potential participant dropouts or missing data essential for statistical analysis.

### Ethical considerations

This study, adhering to the Helsinki Declaration and its subsequent amendments, mandates informed consent from participants and their legal guardians based on verbal and written details provided. Participants and their legal guardians reserve the right to withdraw at any point, with no obligation to justify their decision and no impact on future treatment. Approval for the study has been granted by the Seoul National University Hospital IRB Review Board (IRB No. H-2210-137-1374). The investigators anticipate no discomfort for the subjects from the tests and tasks involved, with no short- or long-term risks identified in relation to this study.

### Outcome

We posit that ASD individuals with decreased joint attention, characterized by atypical social gaze patterns, will exhibit unique genetic, structural, and functional neural patterns distinct from ASD individuals with mostly intact joint attention, who demonstrate appropriate social gaze patterns. The differentiation is likely rooted in the connectivity within the visual and social brain pathways. It is anticipated that ASD individuals with decreased joint attention will possess SNPs associated with the visual pathway. Furthermore, individuals with greater RRB than SC impairment are expected to exhibit less impairment in social gaze ability. Conversely, participants with a higher SC impairment relative to RRB are predicted to demonstrate a pronounced deficiency in social gaze ability. A layout of expected outcome table is depicted in Table 2.

**Table 2 Tab2:** Expected outcome table layout

ASD with decreased joint attention	ASD with intact joint attention
**Genetic profile**: SNP component, Unique genes	
**sMRI/DTI**: Cortical features, Volume, Structural connectivity indices	
**rsfMRI**: Connectome gradient, Functional connectivity	
**Clinical/SES profile**: FSIQ, VIQ, SRS, SCQ, CBCL, VABS, DCDQ Parent, Sibling info	
**Social gaze pattern**: Gaze frequency (% Object of interest, % Human, %Other)	

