#### Whole genome sequencing (WGS)

We acquire blood samples from the participant for genomic analyses—we specifically wish to identify all variants associated with ASD and calculate polygenic risk scores for each participant. These methods are important for determining whether different clusters or subgroups of ASD based on social gaze patterns differ at the genetic, blueprint-level; ASD individuals may show varying social gaze patterns based on their entire mutation profile.

Collection and Processing of Peripheral Whole Blood Samples: Each participant will contribute a 3ml sample of peripheral whole blood. These samples will be subjected to genomic DNA extraction and whole genome sequencing, performed with the NextSeq 550Dx System (Illumina, San Diego, CA, USA). The procedure for whole genome sequencing will adhere to an industry standard quality-controlled sequence analysis pipeline and utilize a current reference sequence for the purposes of mapping and variant calling [40].

Identification of single nucleotide polymorphisms (SNPs) and insertions and deletions (indels) will be conducted with HaplotypeCaller and MuTect2 from the GATK package (3.8-0, https://github.com/broadinstitute/gatk/releases), as well as with VarScan2 (2.4.0, https://github.com/dkoboldt/varscan/releases). A variety of databases will be used for the analysis and annotation of variants, including but not limited to, the Online Mendelian Inheritance in Man (OMIM), the Human Gene Mutation Database (HGMD), Clinvar, dbSNP, 1000 Genomes, the Exome Aggregation Consortium (ExAC), the Exome Sequencing Project (ESP), the Korean Reference Genome Database (KRGDB), Autism Speaks MSSNG resource, and the Simons Simplex Collection (SSC). Variants will be classified following the standards and guidelines set forth by the American College of Medical Genetics (ACMG) [41]. Following annotation, the sequencing data will undergo additional processing to compute polygenic risk scores for ASD of the top SNPs after thresholding the SNP component [42]. Such computation aims to aid in differentiating between individuals with Autism Spectrum Disorder (ASD) based on their distinct genetic susceptibility or polygenic risk variability.

The different types of data for comparison between subgroups of ASD are listed in Table 1.

**Table 1 Tab1:** Different types of data acquired in proposed study

Data Types	Case Report Form	Neuro-psychiatric Tests	Brain Imaging	Whole Genome Sequencing	Video

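### The visual-pathway SNP prediction and the unique-genes entry are presence statements that a random split of 60 children would very likely also produce, so they cannot by themselves show that the clusters differ genetically

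*Protocol article*

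**What the plan says.** The Abstract of the protocol article makes genetic distinctness one of three claims for the gaze-based clusters, beside clinical and neurological distinctness. Four places bear on how it will be judged.

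- **Outcome, text.** The one specific genetic prediction is: "It is anticipated that ASD individuals with decreased joint attention will possess SNPs associated with the visual pathway". The section names no gene set and no size of difference from the other cluster.
- **Outcome, Table 2.** The genetic row reads "SNP component, Unique genes". The table is introduced with the words "A layout of expected outcome table is depicted in Table 2". The article does not define when a gene counts as unique.
- **Whole genome sequencing (WGS).** The aim is to "identify all variants associated with ASD and calculate polygenic risk scores for each participant". The scores are described as "polygenic risk scores for ASD of the top SNPs after thresholding the SNP component", which links the SNP component of Table 2 to a number for each child.
- **Comparison between good gaze response group and poor gaze response group.** The listed elements are socio-demographic and clinical characteristics, gaze patterns, structural MRI and resting-state fMRI. No genetic measure is listed.

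**The concern.** A statement that one group carries certain variants, or that some genes appear in one group only, is evidence of a group difference only if it would be unlikely when the grouping is arbitrary. Whole-genome sequencing of 60 children will record many variants carried by one or a few of them. Wherever the dividing line is drawn, such variants tend to fall on one side of it. Likewise, a set of visual-pathway SNPs of any size will usually have at least one carrier in either cluster.

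The study asks whether joint-attention clusters are genetically real. If the visual-pathway prediction is judged by presence, it is very hard to refute, and a list of unique genes could be read as support when chance alone would supply one.

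**Working it through.** **Inputs from the article.** Planned total 60 (Power calculation – sample size estimation). Two clusters with sizes not fixed (Social Gaze-based semi-supervised clustering analysis). The assay is whole genome sequencing. The article gives no expected genetic result, so there is no figure to reproduce.

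**Inputs that are assumptions.** Cluster sizes (30/30, 45/15, 48/12), carrier counts, carrier frequencies and numbers of genes. Unique is taken to mean carried by at least one child in one cluster and by none in the other.

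**1. A gene with m carriers falls wholly in one cluster.** For a random split into sizes a and b,

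P = [C(a,m) + C(b,m)] / C(60,m).

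- 30/30, m = 2: (435 + 435)/1,770 = 0.49
- 30/30, m = 3: (4,060 + 4,060)/34,220 = 0.24
- 30/30, m = 4: (27,405 + 27,405)/487,635 = 0.11
- 45/15, m = 2: (990 + 105)/1,770 = 0.62
- 45/15, m = 3: (14,190 + 455)/34,220 = 0.43
- 45/15, m = 4: (148,995 + 1,365)/487,635 = 0.31

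For m = 1 the probability is 1.00 at any split.

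**2. Both clusters show at least one unique gene.** Count only G genes with a single carrier each, treated as independent, and let p be the smaller cluster's share:

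P = 1 − p^G − (1 − p)^G.

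| G | 30/30 | 45/15 | 48/12 |
|---|---|---|---|
| 5 | 0.94 | 0.76 | 0.67 |
| 10 | 0.998 | 0.94 | 0.89 |
| 20 | about 1 | 0.997 | 0.99 |

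**3. How long the lists would be.** If each child carries a qualifying variant in a gene with probability q, the expected number of unique genes per cluster of 30 is G × [1 − (1 − q)^30] × (1 − q)^30. With q = 0.005 and G = 50 this is 50 × 0.140 × 0.860 = 6.0. With q = 0.02 and G = 500 it is 500 × 0.455 × 0.545 = 124. A simulation (2,000 random splits per setting, q from 0.005 to 0.05, G from 50 to 500) gave means in the same range of about 6 to 124. Both lists were non-empty in at least 99.7% of splits.

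**4. A cluster possesses a visual-pathway SNP.** For K independent SNPs with carrier frequency q in a cluster of n, P(at least one carrier) = 1 − (1 − q)^(nK).

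- n = 30, K = 1: 0.26 at q = 1%, 0.79 at 5%, 0.96 at 10%
- n = 30, K = 10: 0.95 at q = 1%, about 1 at 5%
- n = 12, K = 10: 0.70 at q = 1%, 0.998 at 5%

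The prediction could readily fail only for a very short list of rare SNPs.

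**5. Contrast with a score.** A two-sided comparison of a per-child mean score at 0.05, 30 against 30, has a controlled false-positive rate. Its power is 0.12, 0.49 and 0.87 for standardised differences of 0.2, 0.5 and 0.8. That is modest for small effects, but the result can go either way.

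**The case against.** The strongest reply is that Table 2 is a results layout with no decision rule, that the visual-pathway sentence is hypothesis prose, and that operational definitions belong in documents not shown. The section also opens by positing patterns that differ from those of the other cluster, so the sentence may be meant comparatively. These points have weight: nothing says that a non-empty list will count as success. But the presence wording is what the article prints for its only specific genetic prediction, and an analysis that applied it literally would inherit the weakness. Exploratory status excuses low power, but not a criterion that chance meets.

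Three stronger readings are tempting and not supported:

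- **The whole genetic outcome is uninformative.** The same Table 2 cell names the SNP component, which the WGS section ties to a polygenic score per child. That score can be compared between clusters with a proper null. The Abstract also says that genetic predisposition will be compared, and the comparison section's list is introduced as what the elements include, so its silence on genetics does not prove that no comparison is planned.
- **The outcome is met under any split.** It is very likely, not certain. With five single-carrier genes and a 48/12 split, both lists are non-empty with probability 0.67, and a single 1% SNP appears in a cluster of 30 with probability 0.26.
- **The named test is invalid for carrier data.** The article says "To compare categorical variables, the chi-squared test will be utilized", but ties this to no carrier table and does not say whether a continuity correction applies. For 4/30 against 0/30 the uncorrected test gives p = 0.038, the Yates-corrected test 0.12 and Fisher's exact test 0.112. The apparent problem depends on a version that the article does not specify.

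**Conclusion.** The point holds for two elements: the visual-pathway prediction as worded, and the unique-genes entry. In a random 30/30 split, genes with one to four carriers are confined to one cluster with probability 1.00, 0.49, 0.24 and 0.11, and less even splits raise the last three. With whole-genome data, both elements would very likely appear with meaningless clusters, so neither can by itself support genetic distinctness or the visual-pathway prediction.

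General genetic distinctness can still be tested through the polygenic score. Because that score is built for ASD as a whole, it leaves the visual-pathway prediction without a matching measure.

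The per-gene probabilities rest only on the total of 60, the assumed cluster sizes and a random split. The list lengths and possession probabilities also rest on assumed carrier frequencies and gene counts, for which the article gives no figures; hence the ranges.

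**What to change.** 1. In Outcome, restate the visual-pathway prediction as a between-cluster difference in one gene-set burden or score per child. Name the gene set before anyone sees the cluster labels, and take the p-value from random permutation of those labels.
2. Name the ASD polygenic score as the second genetic comparison.
3. Add both to the elements listed in the section comparing the good and poor gaze response groups.
4. In Table 2, mark unique genes as descriptive only.

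An exact test for sparse carrier tables is at most a minor addition.

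The cost is agreeing the gene list in advance and a short script. No extra sequencing or participants are needed.

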## Discussion

Prompted by a clinical demand for ASD subclassification based on distinct neurobiological and behavioral traits, this study is the first to prospectively gather multi-modal data of ASD individuals, utilizing objective behavioral biomarkers for group clustering. Greater comprehension of ASD types, characterized by their unique behavioral anomalies and underlying mechanisms, is essential for devising patient-specific treatments. Ignoring the interplay of patient-specific needs, overt impairments (social-communication or attentiveness to social cues), genetic susceptibilities, and biological-neurological conditions can result in inefficiencies and parental frustration. Our methodology seeks to mitigate these issues by facilitating successful ASD subclassification based on unique behavioral-neurological-genetic patterns.

## Data Availability

The dataset used and/or analyzed during the current are available from the corresponding author on reasonable request.

## Abbreviations

ADOS2: Autism Diagnostic Observation Schedule-2
ASD: Autism Spectrum Disorder
CBCL: Child Behavior Checklist
DCDQ: Developmental Coordination Disorder Questionnaire
DTI: Diffusion tensor imaging
FSIQ: Full Scale Intelligence Quotient
GATK: Genome Analysis Toolkit
IJA: Initiation of Joint Attention
JA: Joint Attention
PCA: Principal Component Analysis
RJA_low_: Low Level Response to Joint Attention
RJA_high_: High Level Response to Joint Attention
rsfMRI: Resting State Functional Magnetic Resonance Imaging
SCQ: Social Communication Questionnaire
SNP: Single Nucleotide Polymorphism
SRS: Social Responsiveness Scale
sMRI: Structural Magnetic Resonance Imaging
VABS: Vineland Adaptive Behavior Scales
VIQ: Verbal Intelligence Quotient
WPPSI: Wechsler Preschool and Primary Scale of Intelligence
YSMS: Yonsei Seoul Multi-modal Subclassification
